## 5 STUDY DESIGN

### 5.1 Overall Design

This is a multi-site, stepped wedge cluster randomized controlled trial to evaluate the effect of the PT-AWV intervention on AWV and preventive health services use. The study will take place in 24 primary care practices around the United States (8 community-based, 8 academic, and 8 safety net practices). Recruitment and intervention implementation occur at the practice level. We hypothesize that the intervention will increase uptake of AWVs and use of preventive health services.

The **stepped wedge cluster design** is a pragmatic study design that includes an initial control period in which no clusters receive the intervention. Randomized clusters cross to the intervention condition at regular intervals, and there is a period at the end of the study where all clusters have been exposed to the intervention. Data are collected throughout the study so that each cluster contributes to both the control and intervention periods.[^155-157^](#_ENREF_155) The intervention will be implemented sequentially over 15 months, with 4 clusters of 6 practices each switching from control to intervention every 3 months. For each practice, intervention implementation will occur over a 6-month period. All practices will complete intervention implementation 15 months after the onset of intervention implementation in the first set of practices.

Outcomes for the primary and secondary endpoints will be assessed through EHR data extractions. The DARTNet Institute (co-investigator [name], PhD) will serve as the data coordinating center for the study. Co-investigator [name] at the American Academy of Family Physicians National Research Network (AAFP NRN) will clean, de-identify and create flags to develop analytic datasets. The AAFP NRN has established contracts and agreements with the DARTNet Institute that enable [name] to access DARTNet’s data. [name] will deliver limited datasets to investigators at the University of California, Los Angeles for analyses.

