## 10 STATISTICAL CONSIDERATIONS

### 10.1 Statistical Hypothesis

- ***Primary Endpoints***:

We hypothesize that the intervention (PT-AWV intervention) will result in:

- 1. greater AWV utilization (% of eligible patients completing an AWV or IPPE in the past 12 months) at 12, 18 and 24 months after intervention implementation
  2. patients being up to date on a greater percentage of their total number of recommended services (of a maximum of 12 recommended services per patient) at 12, 18 and 24 months after intervention implementation;

We also hypothesize that the PT-AWV intervention will reduce racial/ethnic disparities in AWV utilization. Alternatively, our null hypotheses are that there will be no difference in AWV or USPSTF and CDC/ACIP-recommended service utilization with implementation of the PT-AWV intervention and that there will be racial/ethnic disparities in AWV utilization.

- ***Secondary Endpoint***(s):

We hypothesize that the PT-AWV intervention will result in a greater percentage of patients who are up to date on each of the individual preventive health services listed in [Section 4.0](#_4_OBJECTIVES_AND) **Table 2**. Alternatively, our null hypothesis is that there will be no difference in utilization in the USPSTF and CDC/ACIP-recommended services examined.

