| ***Composite preventive health score*** |  | >99 | >99 |
| 800 patients / practice |  | >99 | >99 |
| 1200 patients / practice |  | >99 | >99 |
| 1500 patients / practice |  | >99 | >99 |

Our pilot data suggested a decrease in ***racial/ethnic disparities*** in AWV utilization: at baseline, 7.7% of White patients and 4.9% of non-Whites completed AWVs (p=0.09), whereas 6 months post-implementation, 49.8% of White patients and 50.5% of non-Whites completed AWVs (p=0.63).

**Table 5** demonstrates power calculations to detect a 5% reduction in racial/ethnic disparities for AWVs with a sample of 24 practices, ICC=0.05 and type-I error rate α = 0.05. We will have >99% power to detect a 5% reduction in racial/ethnic disparities in AWVs between White and Hispanic patients and >99% power to detect a 5% reduction in disparities between White and Black patients for AWV completion. This calculation assumes the intervention effect is about 10% for White patients and 15% for Black and Hispanic patients, and that about 60%, 20% and 15% of the study population are White, Hispanic, and Black. For the composite preventive health services score power calculation, we further assume that on average each patient is eligible for > 8 preventive health services.

| **Table 5. Power for detecting 5% reduction in racial/ethnic disparities for AWVs and composite preventive health services score, with a type-I error rate α = 0.05 and ICC=0.05, based on patients/practice and baseline rates of outcomes** | | | | |
| --- | --- | --- | --- | --- |
| **Outcome** | **Baseline rate, %** | **Baseline rate, %** | **Power for Black-White disparity reduction, %** | **Power for Hispanic-White disparity reduction, %** |
| ***AWV*** | ***White*** | ***Black/Hispanic*** |  |  |
| 800 patients / practice | 30 | 10 | >99% | >99% |
|  |  | 15 | >99% | >99% |
|  |  | 20 | >99% | >99% |
|  | 40 | 10 | >99% | >99% |
|  |  | 15 | >99% | >99% |
|  |  | 20 | >99% | >99% |
|  | 50 | 10 | >99% | >99% |
|  |  | 15 | >99% | >99% |
|  |  | 20 | >99% | >99% |
| 1200 patients / practice | 30 | 10 | >99% | >99% |
|  |  | 15 | >99% | >99% |
|  |  | 20 | >99% | >99% |
|  | 40 | 10 | >99% | >99% |
|  |  | 15 | >99% | >99% |
|  |  | 20 | >99% | >99% |
|  | 50 | 10 | >99% | >99% |
|  |  | 15 | >99% | >99% |
|  |  | 20 | >99% | >99% |
| 1500 patients / practice | 30 | 10 | >99% | >99% |
|  |  | 15 | >99% | >99% |
|  |  | 20 | >99% | >99% |
|  | 40 | 10 | >99% | >99% |
|  |  | 15 | >99% | >99% |

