***Sensitivity analysis.***

Our main analysis will be a mixed effects logistic regression model with a linear secular time trend. As a sensitivity analysis, we will also explore a piece-wise constant time trend to accommodate a potential non-linear time trend. In addition, we will examine possible time-treatment interaction, to see if the treatment effect increases or decreases over time.

***Secondary objective (examine effect of PT-AWV intervention on reducing racial/ethnic disparities in AWV utilization)***: For each practice and organization, we will summarize use of AWVs by patient race/ethnicity at baseline and every 6 months (up until month 48 of the study) using descriptive statistics. We will also use run charts to illustrate and compare monthly AWV utilization by patient race/ethnicity. **Linear mixed effects models** will be used to directly estimate the percentage change in AWVs and in disparity reduction. The primary covariates in these models are race (Asian, Black/African-American, White, Other) and ethnicity. These models will include fixed effects of treatment, time, treatment-race/ethnicity interaction and patient and practice-level covariates. Other covariates will include: age; gender; insurance coverage (fee-for-service Medicare, Medicare Advantage); # of office visits per year; and practice setting, size, and % of racial/ethnic minority patients. Patients and practices are considered as random effects and piece-wise constant time effect will be constructed to compare the racial/ethnicity disparities in AWV use before and after the intervention, based on the estimates of fixed effects.

***Missing data.*** Mixed effects models accommodate the imbalance of patient data, assuming that they are missing at random. Based on our preliminary data, we expect few missing data for patient age, gender, insurance and number of office visits per year. For missing data on race, we will perform analyses with missing race as a variable and also will impute the race/ethnicity variable.

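### The disparity model lists treatment-by-race/ethnicity but no race/ethnicity-by-time term, so secular change in the gap that is aligned with exposure is credited to the intervention

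*Protocol*

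**What the plan says.** The disparity analysis is the secondary-objective paragraph of Protocol 10.4.2, placed after the sensitivity-analysis text.

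- Fixed effects: "These models will include fixed effects of treatment, time, treatment-race/ethnicity interaction and patient and practice-level covariates".
- Race and ethnicity enter as main effects: "The primary covariates in these models are race (Asian, Black/African-American, White, Other) and ethnicity".
- Time and random effects: "Patients and practices are considered as random effects and piece-wise constant time effect will be constructed to compare the racial/ethnicity disparities in AWV use". The sentence goes on to say that the before/after comparison rests on the estimated fixed effects.
- The only other interaction with time is a sensitivity analysis just above: "we will examine possible time-treatment interaction, to see if the treatment effect increases or decreases over time". That lets the treatment effect change over time. It does not give the gap a time path of its own.
- Layout, from 5.1: "with 4 clusters of 6 practices each switching from control to intervention every 3 months", and "For each practice, intervention implementation will occur over a 6-month period". The synopsis gives a study duration of 39 months.
- Power for the disparity effect, from 10.2 and Table 5: above 99% for a 5-point reduction, "with a sample of 24 practices, ICC=0.05 and type-I error rate α = 0.05".
- The null in 10.1 includes the statement that "there will be racial/ethnic disparities in AWV utilization".

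**The concern.** With the listed terms, the adjusted gap between White and minority patients can change over the study only through treatment-by-race/ethnicity. A stepped wedge puts treated observations later in calendar time by design. The main treatment effect is protected by the common time term, and 10.4.2 gives confounding of time and treatment as a reason for the model. The disparity effect has no matching protection, so its coefficient is largely a before/after change in the gap.

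Equity is in the trial's title, and the disparity effect has its own power table. Because the nominal power is very high, even a small bias would be statistically significant. The Background reports overall AWV uptake rising from 7.8% in 2011 to 24% in 2017, so secular movement in uptake is expected. Whether the gap between groups was moving is not reported.

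**Working it through.** **Inputs from the Protocol.** 24 practices; 4 steps of 6, three months apart; 6-month implementation; 39 months; 60% White, 20% Hispanic, 15% Black; a 5 pp gap reduction (10 pp in White, 15 pp in Black and Hispanic patients); α = 0.05.

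**Assumptions.** Two-sided test; switch at the start of implementation (months 0, 3, 6, 9) or at its end (6, 9, 12, 15); 1 or 12 months of pre-switch data; a linear secular gap trend λ. The practice intercept cancels in the within-practice gap, so the ICC drops out.

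**1. Reproducing Table 5 (800 per practice, White 50%, Black 20%, no race-by-time).** Take five three-monthly cross-sections (months -3 to 9) and, for each group, the larger of the baseline and post-intervention binomial variances.
- Variance of one practice's gap: 0.25/480 + 0.2275/120 = 0.002417, so SD 4.92 pp.
- There are 60 treated and 60 control practice-periods: SE = 4.92 × √(1/60 + 1/60) = 0.90 pp.
- Power = Φ(5/0.90 - 1.96), about 99.98%. This agrees with the stated >99%.

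**2. Bias in the listed model.** If the gap closes by λ per month with no differential effect, an unweighted fit gives

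estimated reduction = λ × (mean month, treated - mean month, control).

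For switches at 0, 3, 6, 9 and data up to month 39:
- Treated: 39, 36, 33 and 30 months per practice, with means 19, 20.5, 22 and 23.5. Overall mean 2910/138 = 21.1.
- Control, 1 pre-month: mean 50/22 = 2.3. Control, 12 pre-months: mean -258/66 = -3.9.
- Differences: 18.8 and 25.0 months (19.3 and 25.1 if the switch is at completion).

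At λ = 1 pp/year:

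| Data fitted | Difference in mean month | Spurious reduction, unweighted | GLS-weighted |
|---|---|---|---|
| to month 39 | 18.8–25.1 | 1.6–2.1 pp | 1.66–2.12 pp |
| to month 15 or 21 | 6.3–15.8 | 0.5–1.3 pp | 0.65–1.37 pp |

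With race-by-time added, linear or categorical, the bias from a linear trend is 0. Over 39 months a trend of 2.4 to 3.0 pp/year would by itself produce the planned 5 pp.

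**3. Simulation with no true differential effect.** 800 per practice, Black versus White, 14 three-monthly cross-sections, gap SD between practices 3 pp (assumed), 150 runs per scenario, cluster-robust test.

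| Assumed narrowing, pp/year | Estimate, listed model | Rejections | Rejections with race-by-period |
|---|---|---|---|
| 0 | -0.1 | 3% | 5% |
| 0.5 | 0.8 | 22% | 5% |
| 1 | 1.7 | 76% | 5% |
| 2 | 3.5 | 100% | 5% |

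With race-by-period, every mean estimate is within 0.2 pp of zero.

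**4. Cost of the extra term (800 per practice, Black–White).** Monthly data from month -12, treated as independent, at baseline rates: gap variance 0.25/480 + 0.16/120 = 0.001854, SD 4.31 pp.
- No race-by-time: 6 × 138 = 828 treated and 6 × 66 = 396 control practice-months. SE = 4.31 × √(1/828 + 1/396) = 0.26 pp.
- Linear race-by-time: 0.43 pp.
- Categorical race-by-time: only months 0 to 8, when treated and control practices coexist, carry information. Within-month sum of squares = 3 × (4.5 + 6 + 4.5) = 45. SE = 4.31/√45 = 0.64 pp.

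Even at 0.64, 5/0.64 - 1.96 is about 5.8, so power exceeds 99%. With the five cross-sections of step 1 the sum of squares is 15:
- Black–White, larger variance: SE = 4.92/√15 = 1.27 pp, power 97.6%.
- Black–White, baseline variance: SE = 4.31/√15 = 1.11 pp, power 99.4%.
- Hispanic–White, larger variance: power 99.3%.

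If the gap also varies between practices (assumed SD 3 to 10 pp), Black–White power on the larger variance is 92% to 87%. Adding practice-by-period variation (assumed SD 3 to 5 pp) can take it as low as 60%.

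**The case against.** The best counter-argument is the piece-wise sentence. A time effect common to all groups cannot by itself compare disparities between periods, so the authors may have meant it to be race-specific, and an analysis plan that is not shown may say so. It follows that the text cannot be read as proof that time will be common to all groups. But the Protocol gives an explicit list of fixed effects and says that the comparison rests on them, and that list has no race-specific time effect. This is a stated set of terms, not a detail left open.

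Stronger readings that a reader might infer, and that the documents do not support:
- *Every secular change in the gap is credited to the intervention.* Only the part correlated with exposure loads on the interaction.
- *The trial will overstate its effect by about 2 pp.* No secular gap trend is given. The 0.5, 1 and 2 pp/year are assumptions, and the bias may run either way.
- *The primary results are confounded too.* The main treatment effect has its own time term.
- *The wording of the null breaks the test.* The research hypothesis in 10.1 is a reduction in disparities, and the planned interaction addresses that.

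The race-stratified run charts would show a pre-existing drift in the gap, but they do not adjust the estimate.

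**Conclusion.** The concern holds in this form: as listed, the disparity model lets the gap change only through treatment-by-race/ethnicity, so secular gap change aligned with exposure is attributed to the intervention, and a widening gap would hide a benefit. The size is conditional on a trend that the documents do not supply: 1.6 to 2.1 pp per assumed 1 pp/year over 39 months, or 0.5 to 1.4 pp over 15 to 21 months, against a 5 pp target. It also depends on the assumed length of pre-switch data.

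This should be fixed. It touches the secondary objective only, and the correction needs no new data or design change.

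**What to change.** In 10.4.2, add race/ethnicity-by-calendar-time in the same form as the main time effect, or state that the piece-wise time effect is race-specific. Test treatment-by-race/ethnicity in that model. The percentage-point scale is already planned, and a random race effect by practice is not needed to remove this bias.

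Recompute Table 5 for the revised model, stating the number of cross-sections and the assumed variation of the gap between practices. The precision cost is real: the standard error goes from about 0.26 to 0.43 pp (linear) or 0.64 pp (categorical) at 800 per practice. Those figures treat monthly values as independent, which is optimistic for a 12-month look-back outcome. Power for 5 pp stays above 99% on that basis, but may fall below it with fewer cross-sections or a gap that varies between practices.

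As a minor wording correction, restate the null in 10.1 as no change in the White–Black or White–Hispanic difference in AWV utilization. The smallest baseline gap in Table 5's AWV rows is 30 - 20 = 10 pp, so a 5 pp reduction leaves a 5 pp disparity, and the present null would remain true under the trial's own target effect.

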#### 10.4.3 Analysis of the Secondary Endpoints

The secondary endpoints are utilization of the individual preventive health services (listed in [**Section 4** **Table 2**](#_4_OBJECTIVES_AND)). For each practice and organization, we will summarize use of individual preventive health services at baseline and every 6 months until the end of the study using descriptive statistics. We will also use run charts to illustrate the monthly percentage of eligible patients who utilized each preventive health service assessed.

**Linear mixed effects models** will be used to assess the effect of the intervention on these secondary endpoints (**Table 7**). We will perform similar analyses to those described in [**section 10.4.2**](#_10.4.2_Analysis_of).

| **Table 7. Patient cohorts, secondary endpoints, and timing of measurement** | | |
| --- | --- | --- |
| **Cohort** | **Endpoints** | **Time Frame** |
| Of Medicare patients aged 50+, with 1 or more visits in the past 12 months, not deceased: those meeting additional eligibility requirements for each preventive service listed in **Table 4** (e.g., age, gender). * | Utilization of each individual preventive health service listed in **Table 4** (% of patients up to date for each preventive health service) | Monthly |
| ***** HEDIS / CMS inclusion and exclusion criteria will be utilized, as applicable | | |

#### 10.4.4 Analysis of the Tertiary Endpoints

Tertiary endpoints relate to evaluating intervention adoption and implementation by describing facilitators and barriers to adoption through analysis of semi-structured interviews and clinician surveys.

[name] will guide analysis of semi-structured interviews, with the support of a graduate-level research team member with qualitative research method expertise. Two members of the research team will review transcripts, both independently and together to inductively generate codes relevant to pre-defined measures guided by the RE-AIM framework.[^164-167^](#_ENREF_164) Co-investigators and patient partners will participate in selected analyses to ensure the trustworthiness and robustness of the findings. We will use a template coding approach[^168^](#_ENREF_168) to efficiently identify and segment data relevant to pre-defined measures guided by the RE-AIM framework. Case-based matrices[^169^](#_ENREF_169) will help us to refine and synthesize our understanding of modifiable reasons that emerge as obstacles for implementing and sustaining the PT-AWV intervention, strategies for mitigating obstacles, and practice strengths that facilitate implementation and sustainability. Analyses will compare and contrast themes raised in different practice settings. Analyses will be done in ATLAS.ti, a software program for analyzing qualitative data. Clinician survey responses will be tabulated to determine the intervention components being used. The investigate team will use content analysis to analyze free-text responses to survey questions on barriers and facilitators of AWV completion.

#### 10.4.5 Safety Analyses

Not applicable

#### 10.4.6 Baseline Descriptive Statistics

Basic descriptive statistics will be generated to describe including number and type of clinicians in participating practices, and to describe demographics of patients eligible for AWVs: age (means with standard deviations; range), gender (percentages), race/ethnicity (percentages). For each practice and organization, we will summarize use of AWVs, the composite preventive health services score, and individual preventive health services at baseline (Month 0) and every 6 months until the end of the study.

#### 10.4.7 Planned Interim Analyses

Not applicable

#### 10.4.8 Sub-Group Analyses

Subgroup analyses will compare patients with fee-for-service versus Medicare Advantage insurance.

#### 10.4.9 Tabulation of individual Participant Data

Individual participant data will not be listed by measure and time point.

#### 10.4.10 Exploratory Analyses

Exploratory analyses will use ***propensity score analyses*** to examine the effect of AWV use on each of the outcomes. By estimating the probability of receiving an AWV in the post-intervention period, these analyses can account for potential differences among patients who do and do not receive AWVs. Those utilizing AWVs may differ from other patients in substantial ways that might affect the outcomes measured.

## 11 REGULATORY, ETHICAL, AND STUDY OVERSIGHT CONSIDERATIONS

### 11.1 Informed Consent Process

#### 11.1.1 Consent/Assent Procedures and Documentation

***Population cohort***. A waiver of informed consent was obtained for data extractions to assess outcome measures for the population cohort, as it is not feasible to obtain informed consent for all patients in this cohort. Patients will have no direct contact with the study investigators, and the investigators will receive only limited datasets for analyses.

***Semi-structured interview cohort***. A waiver of signed informed consent was obtained for semi-structured interviews with patients, clinicians, and staff. These interviews are low risk and written informed consent would be difficult to obtain as the interviews will not occur in-person.

Information sheets and oral consent scripts have been approved by the UCLA Institutional Review Board (IRB). Participants will be emailed the information sheet for review prior to the interview. For those who are unable to receive the information sheet by email or who did not receive it, a team member will read the oral consent script to participants. This will be done either when the interview is scheduled or immediately before the telephone interview begins.

Both the information sheet and oral consent script contain explanations of the purpose, procedures, and potential risks of the study and of their rights as research participants. Participants will be informed that participation is voluntary and that they may withdraw from the study at any time, without prejudice, and that the quality of their medical care will not be adversely affected if they decline to participate in this study.

Before the interview begins, the interviewer will ask participants if they have questions about the information sheet / oral consent script, and will answer any questions that may arise.

The research is no greater than minimal risk and only involves procedures for which written consent is normally not required outside the research context.

***Clinician survey cohort.*** A waiver of signed informed consent was obtained for clinician surveys. Information regarding the survey will be presented to clinicians immediately before they begin taking the survey (as the first page of the electronic survey). This information will contain explanations of the purpose, procedures, and potential risks of the study and of their rights as research participants. Clinicians will be informed that participation is voluntary and that they may withdraw from the study at any time.

